**serum creatinine (mmol/dL) x 0.0113 = serum creatinine (mg/dL).**

Using each of these individual measurements, the VVR Score at the time of each arterial blood gas measurement will be calculated as follows:

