## Outcome Measures

### Primary Outcome

The primary outcome would be VVR Score at 7days in both arms.

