## APPENDIX 4: Calculation of VVR Scores and VIS Scores

The VIS is calculated in the following manner:

**VIS = dopamine dose (mg/kg/min) + dobutamine dose (mg/kg/min) + 100 x epinephrine dose (mg/kg/min) + 10 x milrinone dose (mg/kg/min) + 10,000 x vasopressin dose (U/kg/min) + 100 x norepinephrine dose (mg/kg/min)**

For patients on no vasoactive support at the time of blood gas measurement, VIS equaled zero.

The ventilation index (VI) is measured as follows:

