**VI = (Ventilator RR) x (PIP - PEEP) x PaCO2 / 1,000**

For patients who were extubated to CPAP at the time of blood gas measurement, VI equaled zero.

For those on High Frequency Ventilation, PIP-PEEP will be replaced by Mean Airway Pressure (MAP) and ventilator RR of 60 (which is the maximum ventilator rate on conventional mechanical ventilation) will be used for the purpose of calculating VI score.

For patients on NIMV, a calculated PIP of 5cmH2O less than the ventilator set PIP will be used to account for attenuation of set ventilator pressures reaching the nares.

The baseline serum creatinine will be subtracted from serum creatinine (Cr) measurement by 72 hours of life which will be labelled ΔCr. For patients in whom 72 hour serum creatinine measurements were less than or equal to baseline, we will record ΔCr = 0. Creatinine will be measured in mg/dL. In our center creatinine is measured in mmol/L. This will be converted to mg/dL to calculate the score as follows:

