**VVR = VIS + VI + (ΔCr x 10)**

**Both VIS and VVR scores have been validated in neonatal population.**

## APPENDIX 5: Comprehensive Study Guideline for Hemodynamic Assessment

[figure not shown]

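### The creatinine conversion in the VVR formula carries units that contradict each other and do not fit the factor 0.0113, which is right only for micromol/L

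*Protocol*

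**What the plan says.** The Primary Outcome section reads "The primary outcome would be VVR Score at 7days in both arms". Appendix 4 of the protocol (Calculation of VVR Scores and VIS Scores) defines the score as "VVR = VIS + VI + (ΔCr x 10"), where ΔCr is the rise from baseline in serum creatinine by 72 hours, set to zero if there is no rise.

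On creatinine units the appendix makes three statements in sequence:

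- The unit the score needs: "Creatinine will be measured in mg/dL".
- The unit the laboratory uses: "In our center creatinine is measured in mmol/L".
- The conversion: "serum creatinine (mmol/dL) x 0.0113 = serum creatinine (mg/dL").

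On drug units, the VIS line begins "VIS = dopamine dose (mg/kg/min) + dobutamine dose (mg/kg/min) + 100 x epinephrine dose (mg/kg/min"). It continues with "10 x milrinone dose (mg/kg/min") and "10,000 x vasopressin dose (U/kg/min"), and ends with norepinephrine, also per mg and with weight 100.

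**The concern.** The laboratory unit is per litre and the conversion formula starts from a per-decilitre unit, so the two lines cannot both describe the same input. Moreover, 0.0113 does not convert either unit to mg/dL. This is the formula for one of the three components of the primary outcome. Two programmers who both follow the text could obtain different scores, and one who rescales the laboratory result to match the printed unit would reduce the renal component to almost nothing. Scores built that way would not be on the scale of the planning mean of 30 (Sample Size Calculation for VVR Scores) or the cut-off of 53 (Analysis).

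The VIS line raises a related but weaker question. Five of its six drugs are labelled in mg/kg/min, in an appendix where the creatinine factor suggests that an m has been printed in place of a micro sign.

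**Working it through.** **Inputs.** From Appendix 4: factor 0.0113, source units mmol/L and mmol/dL, target mg/dL, renal weight 10. From the sample size section: means 30 and 22.5, SD 15, N = 128. From chemistry: creatinine is C4H7N3O, so its molar mass is 4 × 12.011 + 7 × 1.008 + 3 × 14.007 + 15.999 = 113.12 g/mol. Assumed, because the documents give no creatinine values: a rise of 10 to 100 micromol/L.

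**Step 1: the plan's factor.** 1 micromol/L = 113.12 micrograms/L = 0.11312 mg/L = 0.0113 mg/dL. So 0.0113 is correct from micromol/L.

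**Step 2: the factor each possible source unit needs.**

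| Source unit | Factor to mg/dL | Needed ÷ printed 0.0113 |
|---|---|---|
| micromol/L | 0.0113 | 1 |
| micromol/dL | 0.113 | 10 |
| mmol/L (stated laboratory unit) | 11.3 | 1,000 |
| mmol/dL (unit printed in the formula) | 113 | 10,000 |

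**Step 3: effect on the renal term.** Intended points = 10 × rise in micromol/L × 0.01131. Literal points = 10 × (the same rise expressed in the printed unit) × 0.0113.

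| Assumed rise (micromol/L) | Intended points | micromol/dL reading | mmol/L reading | mmol/dL reading |
|---|---|---|---|---|
| 10 | 1.13 | 0.113 | 0.0011 | 0.0001 |
| 20 | 2.26 | 0.226 | 0.0023 | 0.0002 |
| 50 | 5.66 | 0.565 | 0.0057 | 0.0006 |
| 100 | 11.31 | 1.13 | 0.0113 | 0.0011 |

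These are contributions to one infant's score. The effect on the comparison between arms depends on the difference in mean ΔCr, which the documents do not give.

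**Step 4: sample size.** A two-sided t test at alpha 0.05 with a difference of 7.5 and SD 15 needs 63.8 per group for 80% power. That rounds up to 64, or 128 in total, with power 0.801. The stated N is reproduced, and it does not use the conversion.

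**Step 5: the VIS labels.** If infusion rates are recorded in micrograms/kg/min (an assumption), a recorded value x is x/1,000 in mg/kg/min. Literal coding then divides five of the six terms by 1,000. For illustration only, an entry of 2.5 to 20 micrograms/kg/min on a drug with weight 1 would score 0.0025 to 0.02 instead of 2.5 to 20. The vasopressin term is in U/kg/min and keeps its value.

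The planning mean cannot settle whether the mg label is wrong, because the ventilation index alone can reach it: 40 × 15 × 50 / 1,000 = 30, with illustrative ventilator values.

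**The case against.** The strongest reply is that this is a labelling slip without consequence. The factor 0.0113 is exactly the one for micromol/L. If the laboratory reports in micromol/L and staff multiply that figure by 0.0113, the renal term is right. The near-zero results require someone first to rescale the laboratory figure to the printed unit, a step the protocol does not ask for, and nothing shows that scores were computed that way. This stands, and it limits the practical claim.

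A second reply is that a micro sign may have become an m when the formula was copied or the PDF was read. That cannot be excluded, although the Greek delta in the same appendix survived. It would clear the laboratory unit and the VIS labels, but not the conversion: the printed unit would become micromol/dL, still wrong by 10 and still at odds with a per-litre laboratory unit.

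A reader might infer more: that the inotrope and renal parts of the primary outcome both almost vanish, leaving little but the ventilation index. The documents do not support this. The VIS line contains labels, not a conversion. The protocol gives no infusion rates and no second VIS definition to test them against, and a planning mean of 30 is no evidence because the ventilation index can supply it. Nor is VIS the only record of inotrope use, since Data Collection and Handling also captures inotrope requirement through the first week.

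It would also be wrong to set one infant's renal points against the planned 7.5-point difference between arm means as if they were the same quantity.

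**Conclusion.** The creatinine conversion is wrong as written, and this follows from arithmetic on any reading of the units: a factor of 1,000 for the stated laboratory unit, 10,000 for the unit in the formula, and 10 if micromol/dL was meant. It sits in the definition of the primary outcome, so it should be corrected rather than left as a typographical matter. Whether any score was affected depends on how the calculation was carried out, which the protocol does not show. The point sizes rest on the assumed rise of 10 to 100 micromol/L.

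The VIS labels are a secondary point held with lower confidence. A 1,000-fold loss in five terms follows only if rates are recorded in micrograms/kg/min and the label is coded literally. All of this concerns scoring units, not any dose given.

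**What to change.** 1. Confirm the unit in which the laboratory reports creatinine. If it is micromol/L, change both creatinine lines in Appendix 4 so that they read micromol/L × 0.0113 = mg/dL.
2. Check the VIS scoring units against the score cited as its source, and correct the mg/kg/min labels if they differ.
3. Check how VIS and VVR were programmed, with a worked example for each term, and recompute any scores derived with other units.

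The cost is a few unit labels and a check of the calculation. No new data are needed, and the sample size stays as it is.

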**VVR = VIS + VI + (ΔCr x 10)**

**Both VIS and VVR scores have been validated in neonatal population.**

## APPENDIX 5: Comprehensive Study Guideline for Hemodynamic Assessment

[figure not shown]

## APPENDIX 6: Adverse event reporting form

### Adverse Event/Severe Adverse Event Reporting Form

Patient ID: \_\_\_\_\_

DOB: \_\_/\_\_/\_\_\_\_

Investigator/name of the person reporting the event: \_\_\_\_\_

#### **Which event is being reported?**

Was the event related to the medical device – (NIRS-monitor)?

Yes ☐

Possibly ☐

No ☐

Do not know ☐

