#### Serious Adverse Event (SAE)

Any adverse event that results in death; is life-threatening, requires prolongation of existing hospitalization, result in persistent or significant disability or incapacity, or requires intervention to prevent permanent impairment or damage.

Medical and scientific judgement should be exercised in determining whether an event is an important medical event. An important medical event may not be immediately life threatening and/or result in death or hospitalization. However, if it is determined that the event may jeopardize the subject and/or may require intervention, to prevent one of the other serious adverse event outcomes listed below, the important medical event should be reported as serious.

Taking into account the frequently severe initial conditions of infants born between 230/7 and 286/7 weeks of GA as well as their high risks of complications, the following morbidities or complications have to be routinely reported as AE ([APPENDIX 6](#)):

- Important medical events that are not already collected in the neonatal CRFs .
- Any worsening of the medical event, if judged as serious and related, even if already collected in the neonatal CRFs.
- All adverse events that are related or possibly related to cerebral NIRS and TNE assessment.
- The following subset of AEs in the infant: even if already reported in the CRF:
  - Blood in one or both ventricles without dilatation (Grade II) (report as AE).

- Blood in one or both ventricles with dilatation (Grade III) (report as SAE).
- Brain intraparenchymal blood- Grade IV (report as SAE).
- Hydrocephalus (report as SAE).
- Cystic PVL (report as SAE).
- Cerebral Atrophy (report as SAE).
- Intestinal perforation/NEC requiring surgery (report as SAE).
- ROP requiring surgery (report as SAE).
- Pneumothorax requiring chest tube (report as SAE).
- BPD (report as SAE).
- Death (report as SAE).
- Mild skin irritation secondary to Cerebral NIRS probe, intact skin with erythema (report as AE).
- Moderate-Severe skin irritation secondary to Cerebral NIRS probe- peeling skin, denuded skin, exudates, blisters (report as SAE).

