#### **Classification of Causality of Adverse Reactions**

|                                        |                                                                                                                                                                                                                                                                                                                                                                                                                       |
|----------------------------------------|-----------------------------------------------------------------------------------------------------------------------------------------------------------------------------------------------------------------------------------------------------------------------------------------------------------------------------------------------------------------------------------------------------------------------|
| Certain                         | Event or laboratory test abnormality, with plausible time relationship to the MUSE trial; cannot be explained by disease or other treatments; response to withdrawal plausible (pharmacologically, pathologically); event definitive pharmacologically or phenomenologically (i.e. an objective and specific medical disorder or a recognised pharmacological phenomenon); or rechallenge satisfactory, if necessary. |
| Probable / Likely               | Event or laboratory test abnormality, with reasonable time relationship to the MUSE trial; unlikely to be attributed to disease or other treatment; response to withdrawal clinically reasonable; rechallenge not required.                                                                                                                                                                                           |
| Possible                        | Event or laboratory test abnormality, with reasonable time relationship to the MUSE trial; could also be explained by disease or other treatments; information on drug withdrawal may be lacking or unclear.                                                                                                                                                                                                          |

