| Unlikely                        | Event or laboratory test abnormality, with a time to the MUSE trial that makes a relationship improbable (but not impossible); disease or other drugs provide plausible explanations.                                                                                                                                                                                                                                 |
| Conditional / Unclassified      | Event or laboratory test abnormality; more data for proper assessment needed; or additional data under examination.                                                                                                                                                                                                                                                                                                   |
| Not Assessable / Unclassifiable | Report suggesting an adverse reaction; cannot be judged because information is insufficient or contradictory; data cannot be supplemented or verified.                                                                                                                                                                                                                                                                |

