##### **Category of the event:**

Life-threatening illness or injury ☐

Prolongation of existing hospitalization ☐

Permanent impairment of a body structure or body function ☐

Necessity of medical or surgical intervention to avoid above mentioned ☐

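### The adverse event form asks about relatedness to the NIRS monitor only, although the safety text also requires reporting of events related to TNE

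*Protocol*

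**What the plan says.** Three parts of the protocol bear on this.

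- **The reporting rule.** Under Serious Adverse Event (SAE), the protocol states that "the following morbidities or complications have to be routinely reported as AE" and refers to Appendix 6. The list that follows includes "All adverse events that are related or possibly related to cerebral NIRS and TNE assessment". Relatedness to either component is thus a ground for reporting.
- **The causality scale.** The section headed "Classification of Causality of Adverse Reactions" defines six classes: Certain, Probable/Likely, Possible, Unlikely, "Conditional / Unclassified", and Not Assessable/Unclassifiable. The first four are worded as a relationship to the MUSE trial as a whole.
- **The form.** Appendix 6 has one relatedness question, "Was the event related to the medical device", which identifies the device as the NIRS monitor. The answers offered are Yes, Possibly, No and Do not know. The other structured items are the event category, whether action was taken, and event status. There is also a free-text description.

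**The concern.** The rule and the form are printed in the same document and do not agree. The rule covers two components and the form asks about one. TNE is a scheduled part of the Multimodal arm, with scans at 18-24 and 66-72 hours (Study Procedure, item 3b), so it needs its own attribution.

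Treatment arm cannot stand in for the missing item. Study Procedure items 2b and 2d allow TNE and cerebral NIRS in the Standard arm at the clinical team's discretion, so infants in both arms may be exposed to either. If attribution to TNE depends on what each reporter chooses to write, the coded safety data will describe NIRS relatedness consistently and TNE relatedness unevenly. The trial is also unblinded, which gives further reason to ask the question the same way every time.

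**Working it through.** No figure in the protocol rests on this point, so the check sets the text and the form side by side.

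| Element | Safety text | Appendix 6 form |
|---|---|---|
| Component to which relatedness is judged | NIRS and TNE (2) | NIRS monitor (1) |
| Object of the causality scale | MUSE trial | NIRS monitor |
| Levels | 6 classes | 4 answers |

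**Step 1: trace a TNE event.** Suppose an event is judged possibly related to a scan and unrelated to the NIRS monitor. Under the reporting rule it must be reported because of that link. On the form, the correct answer to the relatedness question is No. None of the remaining structured items (category, action taken, status) asks about cause. A table built from the coded field would show the event as not related, and only the free-text description could show otherwise.

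**Step 2: trace a NIRS event for comparison.** Mild skin irritation from the probe is answered Yes or Possibly and is coded as the rule intends. The gap is therefore specific to TNE.

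**Step 3: try to map the answers to the classes.** The pairing below is my own reading, since the protocol offers none.

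- Yes could be Certain or Probable/Likely.
- Possibly corresponds to Possible.
- No has no exact counterpart. The nearest class, Unlikely, still leaves a relationship open.
- Do not know could be Conditional/Unclassified or Not Assessable/Unclassifiable.

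Two of the four answers each cover two classes, so the six-class judgement cannot be recovered from the form. The object differs as well: an answer about the monitor is not an answer about the trial.

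**Step 4: exposure.** With 64 infants per group (Sample Size Calculation) and 2 scheduled scans each, the Multimodal arm has up to 64 × 2 = 128 scheduled scans, if every infant has both. Discretionary scans in either arm come on top. This counts occasions on which a TNE-related event could arise. The protocol gives no rate for such events, so no expected number follows.

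**The case against.** The strongest reply is that nothing stops a TNE-related event from being reported. The text imposes the duty, the form has room for a description, and No is a truthful answer to a question about the monitor. Case report forms are still to be devised and all data go into REDCap (Data Collection and Handling), so causality may be recorded on forms that are not shown. With 128 planned infants, free-text reports could be coded by hand. The protocol also attends to handling during scans, through pain and stress scoring and developmental support.

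Much of this stands, and it rules out several stronger readings that a reader might infer:

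- *That the form cannot take a non-serious event.* All four category boxes are seriousness criteria, the last being "Necessity of medical or surgical intervention to avoid above mentioned". But the form is titled for adverse events generally, and no box is said to be mandatory. The text itself assigns the class for listed events, for example "Blood in one or both ventricles without dilatation (Grade II) (report as AE". An entry line or choice under the heading about which event is being reported may also have been lost when the PDF was read.
- *That the six-class judgement must be entered on this form and is therefore lost.* The protocol defines the classes without saying where they are recorded.
- *That the trial would report no TNE-related events.* The reporting rule and the free text both allow for them.

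What the reply does not remove is the mismatch on the printed form. The rule refers to Appendix 6, and the one coded relatedness item there omits a component that the rule names.

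**Conclusion.** The point holds as an inconsistency between a stated reporting rule and the form that serves it. One of the two intervention components has no coded relatedness field, and the field that exists uses four answers that do not convert to the protocol's six classes. TNE relatedness would rest on free text and would be captured inconsistently. It would not be impossible to report.

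This assumes that Appendix 6 is used as printed and that no unseen form or database field already asks about TNE. If one does, the remaining task is only to bring the appendix into line. The relatedness question and its four answers are fully legible, so possible losses in text extraction do not affect this conclusion. The importance is low: it concerns the quality of the safety data and has no bearing on the primary outcome, sample size or analysis.

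**What to change.** Replace the single relatedness question in Appendix 6 with two, one for cerebral NIRS and one for TNE. Answer each on the six classes already defined in the protocol, and word the class definitions so that they refer to the component being judged. State in the safety section that the causality class is recorded there. As an optional clarification, add a not-serious choice beside the four category boxes, so that a blank is not left to mean either non-serious or not completed.

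The cost is one form revision and matching fields in REDCap. No procedures, visits or staff are added. If reports already exist on the present form, their free text should be reviewed once to fill in the TNE item.

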#### **THE EVENT**

##### **When did you become aware of the event?**

Date and time: \_\_/\_\_/\_\_\_\_, \_\_: \_\_

##### **Description of the event:**

---

---

---

---

---

##### **Category of the event:**

Life-threatening illness or injury ☐

Prolongation of existing hospitalization ☐

Permanent impairment of a body structure or body function ☐

Necessity of medical or surgical intervention to avoid above mentioned ☐

**Was any action taken at the event? Yes ☐ No ☐**

***If yes, describe:***

---

---

---

---

---

##### **Event status:**

Resolved ☐

Resolved with sequelae ☐ describe: \_\_\_\_\_

Ongoing ☐

Death ☐

